#### Sintilimab Configured Infusion Destruction Record Sheet

##### (1) Basic Information

Subject No.: \_\_\_\_\_ Initials: \_\_\_\_\_ Cycle \_\_\_\_\_

Planned dose administered: \_\_\_\_\_ mg Actual dose administered: \_\_\_\_\_ mg

Size 100 mg/vial \_\_\_\_\_ vial used: Drug No.: \_\_\_\_\_

##### (2) Drug dispensing records

Dilution date: \_\_\_\_ \_\_\_\_

Dilution start time: \_\_\_\_ Dilution end time: \_\_\_\_

Sintilimab: \_\_\_\_ ml Dilution to 0.9% sodium chloride injection: \_\_\_\_ ml;

Signature of operator: \_\_\_\_\_

##### (3) Drug infusion records

Infusion time: \_\_\_\_ to \_\_\_\_ Signature of operator: \_\_\_\_\_

##### (4) Drug destruction

If you need to destroy at the center, please fill in the destruction information, otherwise, please check: ☐ Not Applicable

Destruction time: \_\_\_\_ Quantity: \_\_\_\_ vials (including empty vials) Signature of destroyer: \_\_\_\_\_

| Subject No.:        |        | Record card of Anlotinib |  |  |  |  |  |  |
|---------------------|--------|--------------------------|--|--|--|--|--|--|
|                     |        | Patient :                |  |  |  |  |  |  |
| 1st treatment cycle | Week 1 | Date                     |  |  |  |  |  |  |
|                     |        | Whether or not to take   |  |  |  |  |  |  |
|                     | Week 2 | Date                     |  |  |  |  |  |  |
|                     |        | Whether or not to take   |  |  |  |  |  |  |
|                     | Week 3 | Date                     |  |  |  |  |  |  |
|                     |        | Whether or not to take   |  |  |  |  |  |  |
| 2nd treatment cycle | Week 1 | Date                     |  |  |  |  |  |  |
|                     |        | Whether or not to take   |  |  |  |  |  |  |
|                     | Week 2 | Date                     |  |  |  |  |  |  |
|                     |        | Whether or not to take   |  |  |  |  |  |  |
|                     | Week 3 | Date                     |  |  |  |  |  |  |
|                     |        | Whether or not to take   |  |  |  |  |  |  |
| 3rd treatment cycle | Week 1 | Date                     |  |  |  |  |  |  |
|                     |        | Whether or not to take   |  |  |  |  |  |  |
|                     | Week 2 | Date                     |  |  |  |  |  |  |
|                     |        | Whether or not to take   |  |  |  |  |  |  |
|                     | Week 3 | Date                     |  |  |  |  |  |  |
|                     |        | Whether or not to take   |  |  |  |  |  |  |

**Precautions:** This table is a record card for the dosing of Anlotinib, which is taken once daily, 1 capsule/dose, before breakfast on an empty stomach. Use for two weeks and stop for one week. If the dose is missed, it cannot be made up within 12 hours of the next dose.

**Registration requirements:** Please fill in the date according to the facts, "Whether or not to take" please tick or "x". The gray part means that the drug will not be taken for one week.

### 3.6.2 Dose adjustment and discontinuation of administration

Anlotinib was discontinued if patients developed haemoptysis. For other grade  $\geq 3$  treatment-related adverse events (TRAEs), anlotinib was reduced to 8 mg, and the dose of chemotherapy was reduced by 25.0% of the last dose. Dose modification of sintilimab was prohibited. Patients experiencing intolerable adverse events that led to a delay or discontinuation of one drug continued treatment with the remaining study drug. Treatment continued until intolerable toxicity occurred or consent was withdrawn. Those who developed progressive disease were permitted to undergo surgery or receive SOC-CRT at the investigator's discretion.

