### **3.5.2 Exclusion criteria**

- 1) Presence of locally advanced unresectable or metastatic disease;
- 2) Participants with known ROS1 fusion-positive or ALK translocations;
- 3)  $\geq$  grade 2 peripheral neuropathy;
- 4) Active autoimmune diseases (known or suspected). Type I diabetes, hypothyroidism requiring only hormone replacement therapy, skin disorders that do not require systemic therapy (e.g., vitiligo, psoriasis, or alopecia areata), or disorders that are not expected to recur in the absence of external stimuli are eligible for enrollment;
- 5) Those requiring systemic treatment with glucocorticoids ( $>10$  mg prednisone equivalent dose per day) or other immunosuppressive drugs within 14 days prior to randomization. Inhaled or topical steroids are permitted in the absence of active autoimmune disease;
- 6) Active hepatitis B/hepatitis C infection and known HIV infection;
- 7) Patients with prior chemotherapy or any other anti-tumor therapy;
- 8) Patients having received the following therapies in the past: anti-PD-1, anti-PD-L1, anti-PD-L2, or anti-CTLA-4 antibodies or any other antibody targeting T-cell co-regulatory pathways;
- 9) Patients who have been treated with anti-angiogenic drugs, such as anlotinib;
- 10) Patients with the presence of uncontrollable hypertension;
- 11) Presence of clinically uncontrollable pleural effusion or abdominal effusion;
- 12) Presence of clinically active diverticulitis, abdominal abscess, gastrointestinal obstruction;
- 13) Have received a solid organ or blood system transplant;
- 14) Diagnosis of other malignancies within 5 years prior to the first dose, excluding carcinoma that have been apparently cured, such as basal or squamous cell skin cancer, superficial bladder cancer, or carcinoma in situ of the prostate, cervix, or

breast;

15) Have active infection requiring systemic therapy;

16) Vaccination within 30 days prior to the first dose (Cycle 1, Day 1);

17) Patients with hemoptysis (>50 mL/day);

18) Patients whose tumors have invaded important blood vessels or who are at risk of hemorrhage during subsequent studies.

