### **3.5.5 Withdrawal Criteria**

Patients can withdraw from the study at any time, without giving a reason.

Patients must withdraw from the study if any of the following events occur:

1) Patient voluntarily withdraws from the study.

2) Subject or his/her legal representative requests to withdraw from the study;

- 3) There are medical or ethical reasons affecting the continuation of the study;
- 4) The investigator determines that withdrawal from the study is necessary in the best interest of the subject;
- 5) The subject loses to follow-up;
- 6) Subject pregnancy;
- 7) Serious violation of the trial protocol (including serious violation of study enrollment criteria).

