## **3.6 Treatment management**

### **3.6.1 Treatment plan**

Sintilimab (200mg fixed dose) iv, d1, q3w + anlotinib 10mg, po, qd1-14, q3w + platinum-doublet chemotherapy, evaluated after 3 cycles of combination therapy and discontinued for 3 weeks (21 days) followed by surgery, which was performed within 4-6 weeks (22-42 days) of the last dose. The time between each study dosing treatment was called a cycle.

A 3-week dosing and observation cycle was established for the trial. Patients who achieved effective disease control, including complete response (CR), partial response (PR), or stable disease (SD), continued treatment until surgery as per the trial protocol (Tumor Assessment Form, according to RECIST 1.1). For patients who experienced intolerable toxicity, disease progression, or requested to discontinue the drug, treatment was terminated. In cases of disease progression confirmed by imaging, the principal investigator (PI) should promptly review and understand the situation. If certain conditions are met, the patient may still be eligible for surgery with the PI's consent: the patient must be able to tolerate the surgery in terms of symptoms or quality of life, be fully informed and willing, and the surgery should be assessed by the treating physician (investigator) as potentially providing a survival benefit. If surgery is not deemed suitable, the patient may instead undergo standard radiotherapy treatment with the PI's consent.

| NSCLC                                                            |                                 |                                    |                        |
|------------------------------------------------------------------|---------------------------------|------------------------------------|------------------------|
| Drugs in the research                                            | Mode of administration          | Frequency                          | Duration of treatment* |
| Sintilimab
(200mg fixed dose)                                 | Intravenous,
over 30 minutes | Day 1
(one cycle every 3 weeks) | 9 weeks                |
| Anlotinib 10mg                                                   | Oral                            | Daily
(2 weeks on, 1 week off)  | 9 weeks                |
| Platinum-doublet
chemotherapy (guideline
recommended drug) | Intravenous                     | Day 1
(one cycle every 3 weeks) | 9 weeks                |

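### Section 3.6.2 names a stop of anlotinib for haemoptysis alone, so a severe treatment-related bleed outside the airway is by default dose-reduced to 8 mg and not stopped

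*Protocol*

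**What the plan says.** Section 3.6.2 sets the dose-modification rules. It begins "Anlotinib was discontinued if patients developed haemoptysis. For other grade" ≥3 treatment-related events, "anlotinib was reduced to 8 mg, and the dose of chemotherapy was reduced by 25.0% of the last dose". The first sentence states no grade. The second makes no exception by type of event and does not separate grade 3 from grade 4.

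The same paragraph adds: "Patients experiencing intolerable adverse events that led to a delay or discontinuation of one drug continued treatment with the remaining study drug". Section 3.6.1 has a general stop: "For patients who experienced intolerable toxicity, disease progression, or requested to discontinue the drug, treatment was terminated". Neither section defines *intolerable*.

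Section 3.5.4 lists termination criteria and section 3.5.5 lists withdrawal criteria. The latter include "There are medical or ethical reasons affecting the continuation of the study" and "The investigator determines that withdrawal from the study is necessary in the best interest of the subject".

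Two other places deal with bleeding. Section 3.2 lists haemorrhage, without limit of site, among the adverse events of special interest. Section 3.5.2, item 18, excludes "Patients whose tumors have invaded important blood vessels or who are at risk of hemorrhage during subsequent studies".

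**The concern.** Anlotinib is the anti-angiogenic part of the regimen, and the protocol treats bleeding as a hazard both at entry and during observation. Its action rule covers only one site. As written, haemoptysis of any grade ends anlotinib, while a life-threatening treatment-related bleed elsewhere (gastrointestinal or intracranial, for example) is assigned a lower dose of the same drug.

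Two things are at stake. The first is the safety of the individual patient, who by default stays on the drug after a severe bleed attributed to treatment. The second is consistency: the two centres named in section 3.4 could handle the same event differently, one stopping and one reducing, and both would comply with the protocol.

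**Working it through.** The protocol states no figure on this point, so the check is a reading of the rules, with one small piece of arithmetic on dose.

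**Step 1. Which rule applies?** Take a treatment-related grade 3 or 4 haemorrhage that is not haemoptysis.
- The first sentence of 3.6.2 does not apply, because the event is not haemoptysis.
- The second sentence applies, because the event is another treatment-related event of grade ≥3. The action is anlotinib 8 mg and chemotherapy down 25%.

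**Step 2. Does any other clause turn that default into an explicit stop?**

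| Route | Where | Why it does not close the gap |
|---|---|---|
| Intolerable event, one drug stopped | 3.6.2 | Allows anlotinib alone to be stopped, but the term is undefined and tied to no event or grade |
| Intolerable toxicity, treatment ended | 3.6.1, 3.6.2 | Same undefined term |
| Patient's request | 3.6.1 | Not a safety rule |
| Grade 3/4 event, treatment not completed | 3.5.4 item 2 | Operates only after a dose adjustment has failed, so it presupposes the 8 mg step |
| Unacceptable drug reaction | 3.5.4 item 4 | The reaction must also be unanticipated; haemorrhage is a listed event of special interest, so it is anticipated |
| Dosing delay over 4 weeks | 3.5.4 item 5 | Triggered by elapsed time; no rule says that a bleed requires a delay |
| Medical reasons or best interest | 3.5.5 items 3 and 4 | Takes the patient out of the study, not off anlotinib alone |

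Stopping is therefore permitted by several routes, and none is an instruction to stop for bleeding.

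**Step 3. Is the default consistent with the rest of the protocol?** Item 18 of 3.5.2 keeps out patients judged to be at risk of haemorrhage. A patient who has had a severe treatment-related haemorrhage has shown that risk, yet the default keeps that patient on the drug. Within 3.6.2, the haemoptysis sentence shows that the authors regard one kind of bleeding as reason to stop outright, whatever its grade. The document gives no reason why a grade 4 bleed at another site should get the milder action.

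**Step 4. What is the difference in dose?** Inputs from 3.6.1: 10 mg daily on days 1–14, three cycles.
- Plan: 14 × 3 = 42 doses; 42 × 10 = 420 mg.
- Cut in each remaining dose under the default: (10 − 8)/10 = 20%. Under a stop: 100%.
- Bleed after cycle 1: 28 × 8 = 224 mg still assigned (224/420 = 53% of plan), against 0 mg.
- Bleed after cycle 2: 14 × 8 = 112 mg still assigned (112/420 = 27%), against 0 mg.
- Bleed after the last anlotinib dose: 0 mg under either rule.

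The two mid-course figures assume that no dose is held or missed. They put 8 mg against 0 mg in milligrams and are not a measure of harm.

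**The case against.** The strongest objection is that an investigator can already stop anlotinib. The sentence in 3.6.2 on stopping one drug for an intolerable event covers a severe bleed, and few clinicians would call a grade 4 haemorrhage tolerable. That stands as far as it goes. A reader might infer that the protocol obliges continued dosing after such a bleed, or that haemoptysis is the only ground on which anlotinib may be stopped. The documents support neither reading. What is missing is a named stop; the specific instruction for the event points the other way.

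A second objection is that listing haemorrhage as an event of special interest calls for observation and recording and does not imply discontinuation. Hypertension and proteinuria are on the same list and fall under the same 8 mg rule. This also stands: the listing alone does not show that the rule is wrong. The argument rests on the contrast with the haemoptysis sentence and with item 18. That grade ≥3 is the right threshold for stopping is a clinical judgement; the documents do not dictate it.

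Four further inferences are tempting and should not be drawn.
- **The grade for the haemoptysis stop is undecided.** The following sentence speaks of other grade ≥3 events, but the haemoptysis sentence carries no grade limit and reads naturally as any grade.
- **Patients with haemoptysis are knowingly admitted.** Item 17 excludes only "Patients with hemoptysis (>50 mL/day"), but item 18 can exclude a patient with smaller active bleeding.
- **The stool occult-blood rule should trigger an anlotinib action.** Flow chart note 8 is a screening step and does not describe a grade ≥3 bleed.
- **The rule endangers the operation.** Surgery follows 22–42 days after the last dose, and coagulation is rechecked in the 7 days before resection.

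**Conclusion.** The point holds in this form: for a treatment-related grade ≥3 haemorrhage outside the airway, the written default is reduction to 8 mg, and no clause explicitly stops anlotinib. It is a stated rule that gives the less safe action, and so is more than an omitted detail. It belongs in the protocol and would not be settled by an analysis plan.

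Its size is limited. For an affected patient it is a 20% cut in the remaining daily doses against a full stop. How many patients that is cannot be estimated, because the documents give no bleeding rate; with 45 planned patients the number is likely to be small. The design, the pathological response rate and the trial's conclusions are not affected.

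The conclusion assumes that the bleed is judged treatment-related, that it is not called intolerable, and that a listed event of special interest counts as anticipated. It is a cheap improvement for patient safety.

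**What to change.** Reword the opening of 3.6.2 as follows:

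> Anlotinib is permanently discontinued for haemoptysis and for any treatment-related grade ≥3 haemorrhage at any site; in the latter case chemotherapy is still reduced by 25%. For other grade ≥3 TRAEs, anlotinib is reduced to 8 mg and chemotherapy by 25%.

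The 25% remains a percentage of the last dose, as now. Section 3.5.4 can stay as it is, because 3.6.2 already lets the other study drugs continue when one is stopped.

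The cost is two sentences by amendment. No visits, tests or data items are added, since adverse events are already graded by CTCAE 5.0 and haemorrhage is already an event of special interest. The downside is less anlotinib exposure in the few patients with a severe bleed.

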### **3.5.3 drop-out/eliminate criteria**

1) Failure to administer the medication in accordance with the dosage, method and course of treatment specified in this research program.

2) Note: Cumulative discontinuation of more than two weeks in a dosing cycle is recorded as drop-out. Failure to use the medication in accordance with the provisions of the protocol resulting in the inability to conduct efficacy and/or safety evaluations;

3) Serious violation of the protocol: concurrent application of chemotherapeutic agents and/or treatment with modern Chinese medicinal preparations with anti-lung cancer indications while participating in this study.

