### **3.5.4 Termination criteria**

1) Disease progression;

2) Grade 3/4 adverse events failure to complete treatment after dose adjustment according to the trial protocol;

3) Death;

4) Occurrence of unanticipated and unacceptable adverse drug reactions;

5) Delayed dosing for >4 weeks. Serious violation of the trial protocol (including serious violation of study enrollment conditions).

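### Section 3.6.2 cuts anlotinib and chemotherapy after any non-haemoptysis grade ≥3 related event, whichever drug caused it, and no rule ties a sintilimab hold to a severe immune-related event

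*Protocol*

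**What the plan says.** The regimen in section 3.6.1 is "Sintilimab (200mg fixed dose) iv, d1, q3w + anlotinib 10mg, po, qd1-14, q3w + platinum-doublet chemotherapy", for three 3-week cycles before surgery.

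Section 3.6.2 sets the dose rules. Haemoptysis stops anlotinib. For all other grade ≥3 treatment-related events, "anlotinib was reduced to 8 mg, and the dose of chemotherapy was reduced by 25.0% of the last dose. Dose modification of sintilimab was prohibited". The next sentence is "Patients experiencing intolerable adverse events that led to a delay or discontinuation of one drug continued treatment with the remaining study drug".

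The routes by which sintilimab could be stopped are spread over several sections:

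- **3.6.1:** treatment is terminated for intolerable toxicity. Section 3.6.2 also makes intolerable toxicity an end point of treatment.
- **3.5.4:** termination for "Grade 3/4 adverse events failure to complete treatment after dose adjustment according to the trial protocol", for "Occurrence of unanticipated and unacceptable adverse drug reactions", and for "Delayed dosing for >4 weeks".
- **3.5.5:** compulsory withdrawal for medical or ethical reasons that affect continuation (item 3), or when "The investigator determines that withdrawal from the study is necessary in the best interest of the subject" (item 4).

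Section 3.2 makes safety a primary endpoint and names immune-mediated pneumonia, cardiomyopathy and endocrine disorders for special attention. Section 6.6 defines immune-related events and lists their terms, but gives no management rule. Section 6.4 grades relatedness to the test drug, in the singular, on five levels.

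**The concern.** The regimen has four components with different toxicities, but the grade ≥3 rule has one response: reduce anlotinib and chemotherapy. A grade 3 pneumonitis or hepatitis that the investigator attributes to sintilimab alone is still a treatment-related event and still triggers both cuts. The only instruction specific to sintilimab is a prohibition, and the sections on immune events contain no hold or stop criterion.

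Two things are at stake. The first is patient safety: whether a patient is re-exposed after a severe immune event depends on individual judgement and may differ between patients and between the two sites. The second is the regimen under test: cuts to drugs that did not cause the event change the treatment whose pathological complete response rate is being estimated.

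This is not a detail left for the statistical analysis plan. Dose rules belong in the protocol, and this protocol has a section for them.

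**Working it through.** **1. Does any rule require a sintilimab hold or stop because a severe immune-related event has occurred?**

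| Provision | What it does | Triggered by a grade ≥3 immune event as such? |
|---|---|---|
| 3.6.2, ban on modification | Keeps the dose at 200 mg; best read as no dose reduction | No |
| 3.6.2, delay or stop of one drug | Says that the remaining treatment continues; names no drug, grade or event type | No; permits a hold |
| 3.6.1 and 3.6.2, intolerable toxicity | Ends treatment | No; undefined, not tied to grade or cause |
| 3.5.4 item 2 | Stops when treatment cannot be completed after protocol dose adjustment; the only stated reductions are to anlotinib and chemotherapy | No |
| 3.5.4 item 4 | Stops for unanticipated reactions | Unclear; 3.2 names several immune events in advance |
| 3.5.4 item 5 | Caps a delay at 4 weeks | No; does not start a delay |
| 3.5.5 item 3 | Compulsory withdrawal for medical reasons | No; the reasons are not specified |
| 3.5.5 item 4 | Withdrawal in the patient's best interest | No; investigator's judgement |
| 6.6 | Definition and term list | No |

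Several provisions allow sintilimab to be stopped, and some require it once a judgement has been made. None attaches to grade or immune cause.

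**2. Does any rule limit the anlotinib and chemotherapy cuts to events that those drugs caused?** No. The condition in 3.6.2 is grade ≥3 and treatment-related, and 6.4 does not ask for relatedness drug by drug.

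**3. Size for one patient.** Inputs: the doses and schedule in 3.6.1 and the reductions in 3.6.2. Assumptions: the cut applies from the next cycle, all other doses are given as planned, and no delay, stop or withdrawal provision is used.

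Planned totals:
- Anlotinib: 3 × 14 days × 10 mg = 420 mg.
- Chemotherapy: 3 full doses.
- Sintilimab: 3 × 200 mg = 600 mg.

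Event in cycle 1:
- Anlotinib: 14 × 10 + 2 × 14 × 8 = 140 + 224 = 364 mg. Loss 56/420 = 13.3%.
- Chemotherapy: (1 + 0.75 + 0.75)/3 = 83.3%. Loss 16.7%.
- Sintilimab still scheduled: 2 × 200 = 400 of 600 mg.

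Event in cycle 2:
- Anlotinib: 2 × 14 × 10 + 14 × 8 = 280 + 112 = 392 mg. Loss 28/420 = 6.7%.
- Chemotherapy: (1 + 1 + 0.75)/3 = 91.7%. Loss 8.3%.
- Sintilimab still scheduled: 200 of 600 mg.

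Event in cycle 3: no preoperative dose remains, so neither the cut nor a hold has any effect before surgery.

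The protocol gives no rate of severe immune-related events. The number of patients affected and the effect on the response rate are therefore not estimated.

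**The case against.** The strongest reply is that the protocol already has mandatory stops. Section 3.6.1 ends all treatment for intolerable toxicity, without requiring a prior dose adjustment or an unanticipated reaction, and 3.5.5 item 3 compels withdrawal for medical reasons. In a paragraph that has just set dose reductions, and with sintilimab given at a fixed dose, the ban on modification most naturally forbids a smaller dose; the next sentence foresees delay or discontinuation. On this reading clinicians can and would hold sintilimab. The uniform cut is also partly defensible: attribution in a four-drug regimen is uncertain, and several terms in 6.6, such as diarrhoea, raised transaminases and rash, are not specific to one drug.

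Most of this stands, and it rules out two stronger readings that a reader might infer:

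- **That the protocol forbids holding sintilimab or mandates re-exposure.** It does neither. The decision is left to judgement.
- **That sparing anlotinib and chemotherapy after a purely immune event would make the patient a drop-out.** The first item of 3.5.3, "Failure to administer the medication in accordance with the dosage, method and course of treatment specified in this research program", can be read that way literally. The rest of 3.5.3 concerns long interruptions, non-use that prevents evaluation, and prohibited concurrent therapy. Nothing shows that clinically justified full dosing would be handled as drop-out.

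The reply does not reach the explicit cut without regard to cause. Nor does it supply a threshold: neither intolerable toxicity nor medical reasons is defined or linked to grade or immune origin.

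**Conclusion.** The point holds in this form: a severe immune-related event as such triggers reductions in anlotinib and chemotherapy, and it triggers no required hold of sintilimab. The general stop rules narrow the gap without closing it.

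Per patient, the loss of planned dose is 6.7% to 13.3% for anlotinib and 8.3% to 16.7% for chemotherapy, with one or two preoperative sintilimab doses still scheduled. These figures rest on the cut starting at the next cycle and on no stop or delay rule being used. They describe what the rule does to planned dosing; they do not measure clinical harm or a change in the response rate.

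It should be fixed, because safety is a primary endpoint and the correction is cheap. It does not make the trial invalid.

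**What to change.** Amend 3.6.2 and 6.4:

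1. Apply the anlotinib and chemotherapy reductions only to grade ≥3 events at least possibly related to those drugs, and record relatedness for each drug in 6.4.
2. State that the ban on modifying sintilimab means no dose reduction, and that delay or discontinuation is allowed.
3. Require sintilimab to be withheld for grade ≥3 immune-related events and permanently stopped for life-threatening ones (grade 4 in 6.2). The investigators should set the exceptions by event type and the criteria for resuming. Controlled endocrine events are an obvious exception, since 6.6 notes that these can usually be managed without immunosuppression. The thresholds are a proposal for the investigators to confirm; they are not taken from the protocol.

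Cost: one text amendment, with no added visits or patients. Two downsides remain. Uncertain attribution means that many mixed events will still trigger the cut, and slightly fewer sintilimab doses may be given.
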